**LIST OF ABBREVIATIONS**

- ACPE The Advisory Committee for Polio Eradication
- AE Adverse Event
- bOPV Bivalent Oral Polio Vaccine
- CI Confidence Interval
- CRA Clinical Research Associate
- CRFs Case Report Forms
- CDC Centers for Disease Control and Prevention
- DCG(I) Drug Controller General of India
- DSMB Data Safety Monitoring Board
- EPI Expanded Programme on Immunization
- GCP Good Clinical Practices
- GMT Geometric Mean Tire
- IB Investigator Brochure
- ICF Informed Consent Form
- ICH International Conference on Harmonization
- IEAG Indian Expert Advisory Group for Polio Eradication
- IEC Independent Ethics Committee
- LAR Legally Acceptable Representative
- mOPV1 Monovalent Oral Poliomyelitis Vaccine Type 1
- mOPV2 Monovalent Oral Poliomyelitis Vaccine Type 2
- mOPV3 Monovalent Oral Poliomyelitis Vaccine Type 3
- SIAs Supplementary Immunization Activities
- sIgA Secretory Immunoglobulin A
- SOPs Standard Operating Procedures
- TCID Tissue Culture Infective Dose
- tOPV Trivalent Oral Poliomyelitis Vaccine
- VAPP Vaccine-associated paralytic poliomyelitis.
- WHO World Health Organization

**Preamble**

With polio eradication making rapid progress, India is one of the four remaining polio-endemic countries and poses a unique challenge for global eradication due to extremely efficient poliovirus transmission . Until April 2005, the Polio Eradication Initiative in India, and globally, has relied exclusively on trivalent oral poliovirus vaccine (tOPV). In 2005, first monovalent type one oral poliovirus vaccine (mOPV1) and then mOPV3 were used for the first time in large-scale campaigns in India to boost humoral & intestinal immunity. In 2009, a new bivalent (type 1+3) OPV (bOPV) was licensed in India, and will be used extensively in the country in 2010, following the recommendations of the Advisory Committee on Polio Eradication (ACPE) [1].

A trial conducted during May 2009 in Moradabad district, Uttar Pradesh, India, showed that > 99% of children 6-9 months of age had detectable antibodies against poliovirus type 1. These results suggest that the strategy of providing mOPV1 through monthly immunization rounds with high coverage is successfully achieving high population immunity. However, these results raise the question of why this high level of population immunity did not interrupt the remaining chains of poliovirus transmission, and children still get infected with wild poliovirus in Uttar Pradesh. Is it possible that insufficient or waning mucosal immunity allows transmission of poliovirus among children who are otherwise protected against paralysis? And, can we boost mucosal immunity in these children to decrease the circulation of virus?

The proposed trial will evaluate mucosal immunity before and after receipt of two different poliovirus vaccine types, in children living in areas at high risk for poliovirus infection. This trial will be conducted after approval from the Indian Regulatory Authorities, Drugs Controller General of India [DCG(I)], and the relevant ethical review committees.

# Background

## Name and description of products:

1. Bivalent type 1 + 3 oral poliovirus vaccine (bOPV) containing at least 106 TCID50 of Sabin poliovirus type 1 and at least 105.8 TCID50 of Sabin poliovirus type 3, respectively, produced from imported bulks by Panacea Biotec Ltd, New Delhi, India.

2. Inactivated poliovirus vaccine (IPV) formulated to contain 40-8-32 D-antigen potency, produced from imported blended bulks by Panacea Biotec Ltd, New Delhi, India.

## Summary of findings from non-clinical studies:

IPV has been used extensively since 12 April 1955, when it was first licensed in the United States after a large field trial demonstrated its efficacy [2, 3]. In the 1960s, an enhanced-potency IPV was formulated that has become the standard formulation used today. Approximately 80 million doses of IPV are used each year, primarily in industrialized countries. The safety profile of IPV is well-characterized, and no serious adverse events have been associated with IPV use. Similarly, the immunogenicity of IPV is excellent with seroconversion rates approaching 100% if administered outside the window with the highest levels of maternally-derived antibody (birth-2 months of age) [2]. In addition, a single dose of IPV following multiple doses of tOPV has been shown to close the remaining immunity gaps very reliably in developing countries [4-6].

bOPV vaccine has been licensed recently in 2009 in Belgium and India. It has been assumed that the efficacy of bOPV would be similar or higher than that of tOPV, but only ~ 300,000 doses were used in Estonia, Lithuania, and Hungary during 1959-1960 [7]. A clinical trial conducted in India during 2009 demonstrated that for both serotypes (1 and 3), bOPV was superior to tOPV and non-inferior to the respective monovalent OPVs [8]. At present the risk of vaccine-associated paralytic poliomyelitis (VAPP) following administration of bOPV is unknown, but assumed to be lower than the risk following tOPV because of the absence of the Sabin Type 2 strain, which is the major cause of VAPP among immunodeficient individuals.

These two vaccines are produced by Panacea Biotec Ltd. and are licensed for use in India by the Drug Controller General of India [DCG(I)].

Trial design justification:

This trial calls for a three-arm design (IPV, bOPV, or unvaccinated) in three age groups, infants aged 6-11 months, children aged 5-6 years, and children aged 10-11 years. A challenge dose with bOPV will be administered to all study subjects to assess mucosal immunity.

This design will provide the first data on mucosal immunity in children living in high risk areas in India. This trial will also assess which polio vaccines are more efficient in boosting mucosal immunity, which would provide an effective barrier to subsequent excretion and community spread of poliovirus. The data from this trial will likely have programmatic implications, especially in determining whether the current age range for SIAs (children aged <5 years) should be re-evaluated. Additionally, the trial will compare different markers of mucosal immunity such as measurement of secretory immunoglobulin A (sIgA) levels in gingival fluid or stools and ELISPOT test, with the gold standard test, which is the measurement of vaccine virus shedding after a challenge with a known dose of OPV. Identifying new surrogate markers of mucosal immunity is important because the challenge test requires high workload and resources, and its use in the post-eradication era may not be possible.

Summary of known and potential risks:

The main serious adverse event associated with oral poliovirus vaccines, including bOPV, is VAPP. Outside the first few months of life, the risk of VAPP is small; approximately 1 case per 1 million doses of tOPV administrated [9, 10], and associated primarily with type 3 and type 2 components of the tOPV. Since bOPV does not contain the Sabin type 2 component, we can assume that the already very low risk of VAPP is even lower following bOPV administration. However, the exact risk of VAPP following bOPV is currently unknown. The only experience with bOPV is available from Estonia, Lithuania and Hungary from 1959-1960. Here the experience is mixed, while Estonia and Lithuania reported no VAPP [10-14], Hungary reported an increase in VAPP [15-17]. The other potentially serious adverse events are anaphylactic reactions. Since OPV and IPV vaccines contain trace amounts of antibiotics, anaphylactic reactions to these antibiotics are possible, but appear to be exceedingly rare. IPV is one of the safest available vaccines, and no systemic serious adverse events are linked to this product. As with all injectable vaccines, minor local adverse events at the injection site are relative frequent.

## Description and justification for the route of administration, dosage, dosage regimen, and treatment period:

At study entry (day 0), subjects will be randomized to one of three study arms. Arm A will be vaccinated with one dose of bOPV administered by the oral route at day 0; arm B will receive one dose of IPV intramuscularly; and arm C will not receive any vaccination. At day 28, all subjects will receive a single dose of bOPV that serves as a challenge dose.

A study from India [18] and a review of mOPV clinical studies is available [19].

## A statement that the trial will be conducted in compliance with protocol, Good Clinical Practice (GCP), and the applicable regulatory requirements:

The study will be conducted in compliance with this protocol, Good Clinical Practice, and all applicable regulatory requirements.

Description of population to be studied:

Healthy children aged 6-11 months, 5-6 years and 10-11 years, who live within a relatively short and easily accessible distance (<30 km) from a study clinic, and do not plan to travel away during the entire 2-month study period.

## References to literature and data relevant to trial, and that provide background for the trial:

The Advisory Committee on Poliomyelitis Eradication (ACPE)

The ACPE has endorsed the need for this trial during the 18-19 November 2009 meeting in Geneva [1].

Polio Research Committee (PRC)

The PRC has reviewed the study protocol in detail during the 10-11 November 2009 meeting in Geneva, has endorsed the study protocol and approved funding.

# Trial Objectives and Purpose

## Mucosal immunity:

- To compare baseline mucosal immunity (through different methods) among three age groups with several degrees of protection acquired through immunization:
  - Infants 6-11 months of age will have received a few OPV doses
  - Children 5-6 years of age will have received multiple OPV doses in campaigns and are expected to have the highest levels of mucosal and humoral immunity
  - Children 10-11 years of age will not have received booster OPV doses for > 5 years. They are expected to have high antibody titers but may have waned mucosal immunity.
- To determine whether one dose of bOPV or IPV significantly reduces excretion of poliovirus types 1 and 3, respectively, following a challenge dose with bOPV, compared to an unvaccinated control arm.
- To determine whether one dose of bOPV or IPV significantly increases sIgA in crevicular fluids and stool samples, and to examine whether the increase in specific SIgA in these specimens is correlated to a reduction in excretion of Sabin poliovirus types 1 and 3 following the challenge with bOPV. This will allow evaluating the use of sIgA as a surrogate test for assessment of mucosal immunity.
- To determine the robustness of the mucosal immune response by study arm and age group, by measuring poliovirus antibody-secreting cells in an ELISPOT-spot assay 7 days after the administration of the study vaccine.

Humoral immunity:

- To determine whether one dose of bOPV or IPV will significantly increase seroprevalence and booster antibody titers compared to unvaccinated children.
- To assess whether one dose of IPV will significantly increase seroprevalence and antibody titers compared to a single dose of bOPV.
- To examine the correlations between antibody titers in blood and shedding of poliovirus after a challenge dose, for each vaccine study arm and age group.
- To examine the correlation between levels of IgA in serum and levels of secretory IgA in crevicular fluids and stool samples, before and after the booster vaccine dose, to gain further understanding on the mechanisms of mucosal immunity against poliovirus.
- To analyze correlations between levels of secretory IgA in crevicular fluids and stools and the ELISPOT test results, to better understand mucosal immunity against poliovirus.

Safety:

- To assess adverse events following vaccine administration.

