# Trial Design

Local community mobilization coordinators (CMCs) working with the Global Polio Eradication Initiative (GPEI) will identify families with children in the target age-group (i.e. 6-11 months, 5-6-years, and 10-11-years). Surveillance Medical Officers (SMOs) will visit households of potential candidate families, explain the study to the parents or guardians, and facilitate transportation to one of the study sites for those interested to participate. Approximately 10 study sites will be chosen in areas identified as high-risk for poliovirus transmission.

At the study site, a physician will conduct a short interview and physical examination. After obtaining informed consent from the parents (and assent from children of age 10-11 years), the study participant will be assigned a study number and allocated to a study arm. For this, the parent or child will select a closed envelope that includes the study arm from a basket. Then a baseline blood sample collected by venipuncture, oral (crevicular) fluid, and stool samples will be collected before vaccine administration.

Note: crevicular fluid will not be collected in the 6-11 month age group because of the absence of teeth.

In a subset of children 10-11 years of age (~175-200 children) a second blood sample will be collected at 7 days by venipuncture for the ELISPOT test.

In all children, at 28 days, another blood sample by venipuncture, another oral (crevicular) fluid sample and a stool sample will be collected before the subjects receives the challenge vaccine (bOPV). Thereafter, at days 3, 7 and 14 stool samples will be collected. And finally, at day 56, another serum sample and oral fluid sample will be collected. At this time, having fulfilled the study requirements, the children will exit the study.

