# Statistics

## A description of the statistical methods to be employed, including timing of any planned interim analysis:

A statistical analysis plan is provided in Annex II

**Humoral immunity**: Chi-square to compare the proportion of children seropositive in each study arm and age group; non-parametric tests to compare the titer distribution among the study arms.

**Mucosal immunity:** Chi-square to compare the proportion of subjects excreting poliovirus type 1, type 2, and type 3 at each collection point among study arms and age-groups; non-parametric tests to compare the median titers of poliovirus shed by individuals at each study arm and age-group.

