# 7. To account for drop-outs and ensure that sufficient subjects will complete all study requirements, we will enrol a total of 990 subjects, 110 per age-group (6-11 mo, 5-6 years and 10-11 years) and per study arm (IPV, OPV and controls).

# ANNEX II

Analytic plan

1. The primary endpoint of the study is reduction in excretion of poliovirus following a challenge dose of bOPV in subjects who have received a single dose of bOPV or IPV.

2. We will use chi-square test to compare the proportion of study subjects that excrete virus/or not following the challenge, in each study arm.

3. To use a conservative measure of p, we will apply a two-tailed test. We will also prepare 95% confidence intervals.

4. We will use non-parametric tests to compare the (median) amount of virus excreted after the challenge in each study arm.

5. We will also use non-parametric tests to measure and compare the distribution of antibody titers in serum (only for those with a positive titer; i.e., >1:8), among study groups and before and after treatment.

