# DOB: ____ \ _____ \ _____ Age: ______ years ______ months Sex: F / M

Religion: H / M / O Father’s occupation:

Father’s education (encircle): Illiterate / Primary / Middle / Tenth / Twelfth / Graduate

Number of people in household (parents & siblings only): ­­

Number of children <5 years in household (study subject):

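### Age groups are not randomised, yet they are compared by unadjusted tests across about 10 sites, so a difference between areas could be reported as a difference between ages

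*Protocol*

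**What the plan says.** The first item under Mucosal immunity in Trial Objectives and Purpose is "To compare baseline mucosal immunity (through different methods) among three age groups with several degrees of protection acquired through immunization". It explains the three groups by their history of oral vaccine and expects mucosal immunity may have waned in the oldest.

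Under Trial Design, "Approximately 10 study sites will be chosen in areas identified as high-risk for poliovirus transmission". Only the arm is allocated by chance: "the parent or child will select a closed envelope that includes the study arm from a basket". Enrolment is fixed at 110 per age group and arm over the whole trial (sample-size section and Annex I). No number per age group is set for a site.

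The Statistics section compares the proportions excreting by chi-square "at each collection point among study arms and age-groups", and uses "non-parametric tests to compare the median titers of poliovirus shed by individuals at each study arm and age-group". It names no stratum or covariate. It also says where the plan is: "A statistical analysis plan is provided in Annex II". Annex II states: "We will use chi-square test to compare the proportion of study subjects that excrete virus/or not following the challenge, in each study arm". It adds two-tailed tests, 95% confidence intervals and non-parametric tests, but no adjustment for site or area.

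The enrolment form in the case report form annex records village, block and CMC area. The Day 0 form records household size and some social data. No stated analysis uses any of them.

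**The concern.** A crude comparison of ages is fair only if the ages are spread alike over places that differ in vaccine coverage or exposure. Nothing in the protocol makes that happen. Community coordinators find the children, families are taken to a site, and the age mix at each site is whatever recruitment produces. If one age group comes more from areas of low excretion, the crude test can find an age difference where none exists, or hide a real one.

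The result has a stated use. The trial design justification says the data will probably bear on whether the age range of the supplementary immunisation campaigns should be re-evaluated. That question leans on the contrast between ages, which is the one contrast in the trial that randomisation does not protect.

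**Working it through.** **The plan's own figure.** Annex I gives 89 per arm and age group for 30% v 10% excretion, two-sided 0.05, power 0.90. Unpooled normal approximation: n = (1.960 + 1.282)² × (0.3×0.7 + 0.1×0.9) / 0.2² = 79 after rounding up. With continuity correction: (79/4) × [1 + √(1 + 4/(79×0.2))]² = 88.7, so 89. Continuity-corrected power at 89 is 0.890, matching the stated 0.89. Also 89×9 = 801 and 110×9 = 990. These figures reproduce and are not in dispute. They are set for arm contrasts within an age group, not for contrasts between ages.

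**Inputs for the check.** From the documents: about 10 sites, two-sided 0.05, 89 completers per age group in one arm, and 3×110 = 330 enrolled per age group over all arms. Assumed, because the documents do not give them: excretion by site and age mix by site. There is no true age effect throughout.

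**Two age groups, by hand.** Spread 10 sites evenly from 20% to 40%. The lower five average 24.4% and the upper five 35.6%. Let one age group draw a share t of its children from the lower five, and the other a share 1 − t.
- t = 0.50: 30.0% v 30.0%, no bias.
- t = 0.65: 0.65×24.4 + 0.35×35.6 = 28.3%, against 31.7%. Difference 3.3 points.
- t = 0.70: 27.8% v 32.2%. Difference 4.4 points.

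The standard error of the difference is √(2×0.3×0.7/n): 0.0687 at n = 89 and 0.0357 at n = 330. The rejection probability is Φ(d/SE − 1.96) + Φ(−d/SE − 1.96).

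| Age mix over areas | n = 89 | n = 330 |
| --- | --- | --- |
| 50/50 | 5% | 5% |
| 65/35 | 8% | 15% |
| 70/30 | 10% | 24% |

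**Three age groups, by simulation.** 10 sites, 3,000 runs per setting, the 3×2 chi-square, and random age imbalance over sites from mild to strong. Type I error of the crude test:

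| Site excretion | n = 89 | n = 330 |
| --- | --- | --- |
| 25-35% | 0.05-0.06 | 0.06-0.07 |
| 20-40% | 0.05-0.07 | 0.06-0.15 |
| 10-50% | 0.06-0.17 | 0.09-0.41 |

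With the same expected age mix at every site, the crude test stays at 0.046-0.052. The site-stratified Cochran-Mantel-Haenszel test stays at 0.04-0.06 in every setting.

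**The case against.** The best defence is that both conditions are assumptions. All sites are in areas chosen as high-risk, the forms are headed with one place name (Moradabad), and coordinators look for all three ages by one process, so differences between sites and in age mix may be small. The age contrast is neither the primary nor a listed secondary endpoint. The protocol allows additional analyses if agreed and assigns high-level statistical work to an academic partner. A fuller analysis plan may also exist.

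Much of this stands as a limit on size. It does not remove the point. The Statistics section names the crude tests by age group and gives Annex II as the plan, so this is a stated method and not a detail left open. Neither the allowance for extra analyses nor the partner's role names an adjustment. The Preamble's finding of over 99% with type 1 antibody concerns serum antibody in infants of 6-9 months. The Preamble itself asks whether mucosal immunity is insufficient despite it.

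Three stronger readings are tempting and are not supported:
- A reader might put every site at exactly 20% or exactly 40%. A 65/35 tilt then gives 27% v 33%, and 70/30 gives 26% v 34%. Rejection is about 14% and 21% at 89 per group, and about 39% and 61% at 330. The arithmetic is right, but such a split is extreme, and the protocol states no day-0 proportion with rates of that kind.
- A reader might infer that the vaccine comparisons are biased too. Arm is randomised, so they are not affected by this.
- A reader might add a household covariate, since the Day 0 form asks "Number of children <5 years in household (study subject". The field does not make clear whether the participant is counted. If so, every infant scores at least one while an older child need not, which ties the covariate to age by construction.

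**Conclusion.** The concern holds as a matter of a stated analysis with a better and inexpensive alternative. It does not show that the age result will be wrong. Bias arises only if areas differ and the ages are spread unevenly over them.

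Under 10 sites spread over 20-40% with no age effect, the false-positive rate is about 5-10% at 89 per age group, the control arm after challenge. That is the natural setting for unboosted shedding. The figure of about 6-24% at 330 per age group applies only if all arms were pooled for a day-0 proportion with similar rates. Values above these need wider site differences together with strong imbalance, or sites split into two extremes.

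A reader might also infer that stratifying would isolate the effect of age or waning. It would not. The objectives explain the groups by their oral vaccine history, and the forms shown have no field for previous doses. Stratification removes confounding by area only, so the age comparison remains observational.

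**What to change.** In the Statistics section and Annex II:
- Stratify every comparison between age groups by study site or recorded area: Cochran-Mantel-Haenszel for proportions and van Elteren for titres. For post-challenge results, do this within arm.
- State how site is obtained. The enrolment and Day 0 forms have no study-site field; it appears only on the adverse event form. Either derive site from village, block or CMC area, or add one field to the Day 0 form.
- Report the age mix by site.
- Label the age comparison as observational, and say that it does not separate age or waning from past oral vaccine exposure.

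A model with the household under-5 count is not recommended.

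Cost: wording in two places, plus one form field or a derivation of site. No extra children or samples are needed. The downside is small: strata with few children add little information.

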# Assessment of Efficacy

## Specification of the efficacy parameters:

Humoral immunity: Sera collected at study entry (day 0) and during the 7-, 28- and 56-day visits, will be examined for the presence (detectable) or absence of neutralizing antibodies to all three poliovirus serotypes. A reciprocal titer of 8 is considered to indicate the presence of neutralizing antibodies. In addition, a change from non-detectable (reciprocal <8) to detectable (reciprocal >8), or from below the highest dilution tested (reciprocal <1448) to the highest dilution tested (reciprocal >1448) will also indicate seroconversion. Although highest titre for neutralizing antibodies is 1024, we are taking end point dilution of half a log higher then 1024. This log of 10.5 is the highest observable titre and is being used because of high titres observed in this highly immunized population.

For participants with detectable antibodies, antibody boosting is defined as a >4-fold increase.

Mucosal immunity: Stool specimens will be collected at 0, 28, 31, 35 and 42 day visits. The samples will be examined for the presence or absence of polioviruses and other enteroviruses. In positive samples, the virus type will be determined following standard protocols from the World Health Organization (WHO) [20]. In addition, the amount (titration) of virus particles will be measured in those samples positive for poliovirus.

Semi-quantitative levels of sIgA in gingival fluid and stool samples will be determined using ELISA. High, medium and low levels will be determined and correlated in each study subject with serum antibody levels and with virus shedding after the challenge (Annex VIII-IX).

Additionally, in a subset of children 10-11 years of age, blood samples collected on days 0 and 7 will be tested to detect the amount of antibody-secreting lymphocytes specific for poliovirus using the ELISPOT technique.

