## The number of subjects to be enrolled, reason for choice of sample size, including reflections on (or calculation of) the power of the trial and clinical justification:

## We estimate a required sample size of at least 801 children to complete the 2-month study (89 per study arm and age group). To account for an estimated drop-out of 15-20%, a total of 990 evaluable children will be enrolled in each arm (110 per age group and study arm). Calculations and justification for sample size estimates are provided in Annex I.

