## The level of significance to be used:

We are seeking to show (a) a reduction in number of subjects excreting vaccine poliovirus following a challenge vaccine dose (bOPV) among those vaccinated with bOPV or IPV compared to the control group; (b) an increase in secretory IgA following vaccination with bOPV or IPV compared to a control group; and (c) an increase in seroprevalence or antibody titers following vaccination with bOPV or IPV compared to a control group.

We use a level of significance of 0.05 (two-tailed test) and a power of 90% to detect the │20%│difference in proportion of subjects shedding vaccine poliovirus after the challenge dose of bOPV(see annex I).

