# ANNEX I

Sample size calculations

1. We are seeking to demonstrate that excretion of poliovirus following a challenge with bOPV is significantly lower in the bOPV or IPV vaccinated groups compared with the control group.

2. Definitions: (a) Significantly decreased defined as a decrease of ׀20%׀ in the proportion of study subjects vaccinated with IPV or bOPV who excrete virus following a challenge dose of bOPV compared with the proportion of control subjects who excrete virus after the challenge.

3. Applying a power of 0.90 (beta) and an alpha of 0.05, the following samples sizes would be required based upon assumed excretion of control and treatment (IPV or bOPV) groups:

| Control group excretion | bOPV or IPV excretion after challenge dose | | |
| --- | --- | --- | --- |
| 0.10 | 0.20 | 0.30 |
| 0.30 | 89 |  |  |
| 0.40 |  | 119 |  |
| 0.50 |  |  | 134 |

5. Using the most likely approach of low excretion in control and treatment groups due to previous exposure to OPV in all subject), we would require a sample of 89 for each study group, for a total of 801 subjects for the 3 study arms and 3 age groups per study arm.

6. With a sample size of at least 89 per study group, we should have a probability of 0.89 or more of estimating any of the differences in excretion of vaccine virus after the challenge dose within a ׀absolute value 20%׀

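### sIgA is to be evaluated as a stand-in for the OPV challenge by correlation alone, which does not measure how well it separates shedders from non-shedders

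*Protocol*

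**What the plan says.** The trial design justification in the protocol's Background sets a test-replacement question. Markers such as sIgA in gingival fluid or stool are to be compared "with the gold standard test, which is the measurement of vaccine virus shedding after a challenge with a known dose of OPV". The reason given is that the challenge is laborious and may not be usable after eradication.

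The Mucosal immunity objectives then name the analysis: see whether the rise in sIgA is correlated with reduced excretion after the challenge. They add: "This will allow evaluating the use of sIgA as a surrogate test for assessment of mucosal immunity".

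Under Assessment of Efficacy, sIgA is read as high, medium or low, and these levels are to be "correlated in each study subject with serum antibody levels and with virus shedding after the challenge".

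The Statistics section says that a statistical analysis plan is given in Annex II. That annex covers proportions excreting, amount of virus excreted and serum titres. It has no item on sIgA. Sensitivity, specificity, an ROC analysis, a cut-off for a positive reading and a minimum acceptable performance appear nowhere in the document.

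**The concern.** Replacing one test by another is a question of accuracy: among children who shed after the challenge, how many would sIgA flag, and among those who do not, how many would it clear? A correlation does not report either figure. Its significance depends on the number of children as well as on the strength of the link, so a weak marker can yield a small p-value in a large enough sample.

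At stake is the conclusion on the surrogate objective. If a significant correlation is the main result, it may be taken as support for using sIgA where the challenge is no longer possible, although classification by sIgA could be poor. The planned samples can answer the accuracy question directly, but the stated analysis does not ask it.

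**Working it through.** **Inputs from the protocol**
- Two-sided alpha of 0.05: "We use a level of significance of 0.05 (two-tailed test) and a power of 90" per cent (level of significance), and "Applying a power of 0.90 (beta) and an alpha of 0.05" (Annex I).
- Numbers: "we would require a sample of 89 for each study group, for a total of 801 subjects" (Annex I), that is, 9 arm-by-age cells of 89. One arm or one age group is 3 x 89 = 267.
- Crevicular fluid is not taken from infants aged 6-11 months (Trial Design), so at most 6 x 89 = 534 children have that reading. Stool can reach 801.
- Shedding: the chosen cell size rests on 30% in controls and 10% in vaccinated children (Annex I).

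**Assumptions, not in the protocol**
- Overall shedding p of 10% to 30%, taken from those two rates.
- A continuous, normally distributed marker with equal variances in shedders and non-shedders.

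**The plan's own figure.** The protocol gives none for the sIgA correlation. Its only power figure is for excretion: "we should have a probability of 0.89 or more of estimating any of the differences in excretion". For 0.30 against 0.10 with n = 89, two-sided, with continuity correction:

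z = (0.20 - 1/89 - 1.96 x sqrt(2 x 0.2 x 0.8/89)) / sqrt((0.3 x 0.7 + 0.1 x 0.9)/89) = 1.227, so power = 0.890.

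This matches. The cell size can be taken as given here.

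**Outcome per child.** Each child is challenged once, so a reduction in excretion is a contrast between arms. The quantity that can be set against a child's own sIgA is shedding, as in the efficacy parameters.

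**Step 1: smallest significant correlation.** r = t / sqrt(n - 2 + t²), with t the 97.5% point on n - 2 degrees of freedom. For n = 89: 1.988 / sqrt(87 + 3.951) = 0.208. For n = 801: 1.963 / sqrt(799 + 3.853) = 0.069.

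**Step 2: convert to accuracy.** Standardised difference d = r / sqrt(p(1 - p)(1 - r²)). AUC = Φ(d/√2). The cut-off with equal sensitivity and specificity gives Φ(d/2) for each. Example, n = 89 and p = 0.2: d = 0.533, AUC = 0.647, sensitivity = specificity = 0.605.

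| Children | Smallest significant r | AUC, p = 10% to 30% | Sensitivity = specificity, p = 10% to 30% |
|---|---|---|---|
| 89 (one cell) | 0.208 | 0.69 to 0.63 | 0.64 to 0.59 |
| 267 (one arm or age group) | 0.120 | 0.61 to 0.57 | 0.58 to 0.55 |
| 534 (all with crevicular fluid) | 0.085 | 0.58 to 0.55 | 0.56 to 0.54 |
| 801 (all, stool) | 0.069 | 0.57 to 0.54 | 0.55 to 0.53 |

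At these cut-offs the share misclassified is one minus the last column: about 36% to 41% in one cell and about 45% to 47% with all 801.

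**Step 3: how easily a weak marker reaches significance.** Take AUC = 0.60, so d = √2 x Φ⁻¹(0.60) = 0.358 and sensitivity = specificity = 0.57. Power is about Φ(d x sqrt(n p(1 - p)) - 1.96). For p from 10% to 30% this is 86% to 99.6% at n = 801, 42% to 77% at n = 267, and 17% to 34% at n = 89.

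**Step 4: pooling over arms.** Suppose vaccination raises sIgA by 1 SD and cuts shedding from 30% to 10%, with no link between sIgA and shedding within any arm. With one third controls, mean shedding is 1/6. The covariance is (1/3)(-2/3)(0.3 - 1/6) + (2/3)(1/3)(0.1 - 1/6) = -0.0444. The variances are 1 + 2/9 = 1.222 for the marker and (1/6)(5/6) = 0.139 for shedding. So r = -0.0444 / sqrt(1.222 x 0.139) = -0.108, beyond the 0.069 needed with 801 children. With a rise of 0.5 SD, r = -0.058, which is not significant. A pooled correlation can therefore arise from the arms alone, but need not.

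**The case against.** The strongest reply is that the protocol promises only to evaluate sIgA. It makes neither a significant correlation nor anything else a rule for accepting it. That stands. A reader might infer that a useless marker would be accepted; the document contains no such decision.

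Second, the near-useless figures need pooling over arms or ages, which the protocol neither states nor excludes for sIgA. The parallel objective on serum titres is set by arm and age group. This also stands: within one cell, a just-significant marker has an AUC of 0.63-0.69, which is modest but not negligible. All the tabulated figures describe the weakest significant result, not an expected one.

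Third, the model uses a continuous normal marker, while the protocol specifies three levels. The figures are therefore indicative. Three levels against shed or not shed form a 3 x 2 table from which sensitivity and specificity follow, so the planned data can give accuracy. It would be wrong to say that they cannot, but the protocol does not ask for it.

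Fourth, an AUC judged only by whether its interval excludes 0.5 could be over-read in the same way. That is right, and the remedy must turn on the size of the estimates.

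Fifth, this may look like detail that belongs in a later analysis plan. That carries less weight: the protocol names a method and says that it serves the surrogate question, and the annex it calls the analysis plan is silent on sIgA.

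**Conclusion.** The point holds in limited form. The protocol asks whether sIgA can stand in for the challenge, and names for this only a correlation, which cannot by itself support such a conclusion.

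Under the assumed 10% to 30% shedding and a normal marker with equal variances, a just-significant correlation is compatible with an AUC of 0.63-0.69 in one cell of 89, 0.55-0.58 with 534 children pooled, and 0.54-0.57 with 801 pooled. How serious this is depends on whether the data are pooled, which is not stated. The documents do not support the reading that the protocol would accept a useless marker, nor that a significant result always means near-chance separation.

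The point touches the surrogate objective only. That objective is neither the primary endpoint nor among the listed secondary endpoints, and the sample size does not rest on it. The change is still worth making.

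**What to change.** In the Mucosal immunity objectives and in Annex II:
- Keep the correlation of sIgA with shedding as a descriptive result.
- Base the surrogate evaluation on the accuracy of day-28 sIgA against post-challenge shedding of the same Sabin type. Report sensitivity and specificity with 95% confidence intervals at the two cut-offs between low, medium and high, and AUC with its 95% confidence interval.
- Report by specimen type (stool, crevicular fluid), and within or adjusted for study arm and age group.
- Set minimum acceptable values in advance, and judge sIgA on the size of the estimates and their lower confidence limits against those values.
- State that statistical significance of a correlation or of an AUC does not alone support replacing the challenge.

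Cost: a few lines of text and a little more analysis. No new samples are needed, since day-28 sIgA and stools at days 3, 7 and 14 after the challenge are already planned. The conclusion on sIgA may turn out less favourable.
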